#### 3.8.7 Progress reports and auditing

Quarterly (once every 3 months) progress reports are provided to the study sponsor. These reports include data quality checks, interim analyses to evaluate protocol efficacy, and summary data. As a part of the larger program, our group participates in weekly communication with other sponsored sites as well as the trial sponsor in order to troubleshoot data collection methods and amend operating procedures as indicated. Auditing of trial conduct is performed by the investigators and the research operations team.

## 4 Planned analyses

### 4.1 Analysis of self-report measures

Primary analyses of self-report data will leverage multi-level modeling to assess the time course of response to LIFUP as well as the difference in response between the active and sham LIFUP groups. The active nucleus accumbens and active caudate conditions will be pooled for the primary analyses, with a second analysis being conducted with only the caudate group vs. sham. The primary variables of interest for these models will be total score on the PVSS and PHQ-14, and EMA variables measuring positive and negative affect. As a secondary analysis, we will re-run this multi-level modeling with the inclusion of the total score on the first eight items of the PHQ-9 (such that total score aligns with PHQ-14 total score) administered one day after each LIFUP session.

Additionally, chi-square analyses will be conducted to assess differences in response rate between sham and active LIFUP, where response will be defined as a 25% or greater score reduction on PHQ-14 or score increase on the PVSS between baseline and the Week 3 survey timepoint (i.e., ~1 week post-LIFUP). We hypothesize that active stimulation of either caudate or nucleus accumbens will be associated with a decrease in PHQ-14 score and increase in PVSS score relative to sham stimulation. This hypothesis is supported by literature showing associations between decreased reward sensitivity in anhedonic depression and hypoactivity in the striatal regions that this study aims to excite (Wang et al., 2021). Similarly, we hypothesize that the EMA data will show an increase in positive affect and a decrease in negative affect after active stimulation relative to sham.

For secondary outcome measures with only two timepoints, repeated measures ANOVA will be used to investigate the effect of time (pre vs. post-LIFUP) and group (active caudate vs. active nucleus accumbens vs. sham).

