### 3.2 Self-report assessments

#### 3.2.1 Primary outcome assessments

The primary self-report outcome measures for this study are the Patient Health Questionnaire (PHQ-14), the Positive Valence Systems Scale (PVSS-21), and the Ecological Momentary Assessment (EMA). The PHQ-14 and PVSS-21 are completed weekly throughout the course of study participation; the schedule of EMA administration is described below and in Figure 1.

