##### 3.2.1.1 Patient Health Questionnaire - 14 item version (PHQ-14)

The PHQ-14 is a modified version of the Patient Health Questionnaire (Kroenke et al., 2010) developed by Cohen, Cohen & Fried (in preparation)^2^ that separates the four compound symptoms from the original PHQ into individual items (e.g., “poor appetite or overeating” was split into two items) and adds two new symptoms: irritability and libido. Score is summarized as a total score aligned with the PHQ-8, where a higher score indicates the severity of depressive symptoms; further information and a copy of the full inventory are available in the Supplementary Method S4 and Supplementary Forms. This assessment was chosen as a primary outcome measure in order to provide information about any changes in overall depressive symptoms in response to LIFUP, given the association between depression symptoms and the LIFUP target regions.

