#### 3.2.2 Secondary outcome measures

An additional set of behavioral questionnaires assessing aspects of anhedonia, depression, anxiety, and general mental wellbeing are collected at baseline and at the end of the study. A list of assessments used for this study is available in Table 2, alongside descriptions of each assessment. Two secondary outcome assessments, The Modified SITBI-R + CSSRS-SR (MSC-SR)^4^ and the Eudaimonic Wellbeing Questionnaire,^5^ were developed by the study team for the purposes of this study; further information regarding the development of these assessments is available in the Supplementary Methods S2, S3. The schedule of administration for these measures is available in Supplementary Table S2, and full assessments are available in the Supplementary Forms.

**Table 2 T2:** A list of the self-report questionnaires, neurocognitive tests, and interviews administered as part of the ILIAD protocol and descriptions of each measure.

**Assessment**	**Assessment type**	**Description**
Ecological Momentary Assessment (EMA)	Primary outcome	Self-reported current mood, environment, experiences, and anhedonic state
Positive Valence Systems Scale (PVSS-21)	Primary outcome	Self-reported index of anhedonia and reward processing, 21 items
Patient Health Questionnaire - modified (PHQ-14)	Primary outcome	Self-reported depression severity, 14 items
Patient Health Questionnaire (PHQ-9)	Secondary outcome/adverse event monitoring	Self-reported depression severity, 9 items
Quick Inventory of Depressive Symptoms (QIDS-SR15)	Secondary outcome	Self-reported depression symptoms, 15-items
Brief Irritability Test (BITe)	Secondary outcome	Self-report irritability measure, 5-items
Modified SITBI-R+CSSRS-SR (MSC-SR)	Secondary outcome	Self-report of suicidal ideation and behavior
Generalized Anxiety Disorder Questionnaire (GAD-7)	Secondary Outcome	Self-reported anxiety symptoms, 7-items
Work and Social Adjustment Scale (WSAS)	Secondary outcome	Self-reported functional impairment of current symptoms in work/school, social life, and family life
World Health Organization (WHO)-5 Wellbeing Index	Secondary outcome	Self-reported current mental wellbeing
Pittsburgh Sleep Quality Index (PSQI)	Secondary outcome	Self-reported recent sleep quality
Snaith-Hamilton Pleasure Scale (SHAPS)	Secondary outcome	Self-reported hedonic experience or positive valence
Apathy Motivation Index (AMI)	Secondary outcome	Self-report index of apathy and motivation

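### In the secondary PHQ re-run, day-after PHQ-9 totals join the weekly PHQ-14 series as if interchangeable, so the within-arm acute time course is confounded with the change of questionnaire

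*Protocol article*

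**What the plan says.** All locations are in the protocol article.

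- **Primary model.** Section 4.1 fits multi-level models with two aims: the time course of response, and the difference between active and sham. For depression, the outcome is the PHQ-14 total: "The primary variables of interest for these models will be total score on the PVSS and PHQ-14". Section 3.2.1 gives the schedule: "The PHQ-14 and PVSS-21 are completed weekly throughout the course of study participation".
- **Secondary re-run.** The same section then says "we will re-run this multi-level modeling with the inclusion of the total score on the first eight items of the PHQ-9", these being "administered one day after each LIFUP session". The reason given for using eight items is "such that total score aligns with PHQ-14 total score".
- **The two forms.** Section 3.2.1.1 says the PHQ-14 "separates the four compound symptoms from the original PHQ into individual items" and adds irritability and libido. On scoring it says "Score is summarized as a total score aligned with the PHQ-8", and it refers to Supplementary Method S4 (not shown) for more.
- **PHQ-9 schedule.** Table 2 labels the PHQ-9 both a secondary outcome and an adverse-event monitoring tool. Section 3.2.2 says of the secondary questionnaires in general that they "are collected at baseline and at the end of the study", and leaves the detailed schedule to Supplementary Table S2 (not shown).

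**The concern.** Matching the content or range of two totals does not make the scores equal. Rating one compound item is a different response task from rating its two halves separately and then combining them. The item count fits 8 + 4 + 2 = 14 (eight base items, four more from the splits, two new symptoms), so four of the eight aligned components are asked differently on the two forms.

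This would matter little if both forms were spread over the follow-up. In the re-run as described, however, the PHQ-9 totals come only from the days after sessions, and the baseline and weekly values are PHQ-14. A level difference between the forms would then look like a drop or rise the day after each session, followed by a rebound at the next weekly survey, in both arms. Time course is one of the two stated aims of these models, and a dip of this kind could be reported as an acute response to stimulation.

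**Working it through.** The article gives no figure to reproduce here. The check is whether the quantities of interest can be estimated, followed by a simulation of what happens when the forms differ.

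**Inputs from the article**
- Sessions on days 1, 3, 5 at the shortest and 1, 5, 9 at the longest (section 3.1.2). PHQ-9 days are therefore 2, 4, 6 or 2, 6, 10.
- PHQ-14 weekly (section 3.2.1).
- Evaluable target of at least 40 (section 2.1), taken as 20 per arm.

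**Assumptions, not in the article**
- Weekly PHQ-14 on days 0, 7, 14, 21, 28, 35.
- Baseline mean 14, between-person SD 3.5, residual SD 2.5.
- Form difference: a shift of 0 to −3 points, or a scale ratio (PHQ-9 to PHQ-14) of 0.8 to 1.2.

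**Step 1: algebra.** Write the mean at occasion t in arm g (0 sham, 1 active) as μ(t) + g·δ(t) + λ·I(t), where I = 1 for PHQ-9 and λ is the offset between forms. Let a be a day-after occasion and 0 the baseline.
- Sham change: μ(a) − μ(0) + λ
- Active change: μ(a) − μ(0) + δ(a) − δ(0) + λ
- Active minus sham: δ(a) − δ(0); λ cancels.

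**Step 2: rank of the design matrix** (same result for both session schedules)

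| Design | Columns | Rank | Within-sham acute change | Active minus sham |
|---|---|---|---|---|
| One arm, free time + instrument | 9 + 1 = 10 | 9 | – | – |
| Two arms, free time by arm + instrument | 9 + 9 + 1 = 19 | 18 | not estimable | estimable |
| Two arms, PHQ-9 also at baseline | 19 | 19 | estimable | estimable |

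With linear time plus an instrument term the rank is 3 of 3. With a pre/post step, a post slope and an instrument term it is 4 of 4. Separation is then possible, but only through the assumed shape of the curve.

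**Step 3: simulation, no treatment effect, 4,000 trials per setting**

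| Shift | Within-sham acute change | Active − sham | Rejection rate, active − sham |
|---|---|---|---|
| 0 | 0.00 | 0.00 | 0.050 |
| −1 | −0.98 | −0.02 | 0.046 |
| −2 | −2.00 | 0.00 | 0.047 |
| −3 | −3.01 | 0.01 | 0.052 |

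The spurious within-arm change equals the shift that was put in. The randomised contrast is untouched.

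**Step 4: unequal sensitivity, true benefit of 3 points**

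| Scale ratio | Expected (3 × ratio) | Simulated active − sham |
|---|---|---|
| 0.8 | −2.4 | −2.40 |
| 1.0 | −3.0 | −2.98 |
| 1.2 | −3.6 | −3.60 |

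Under no treatment effect, rejection at these ratios stayed at 0.048 to 0.054. Unequal scaling changes the size of the acute difference relative to the weekly ones but does not create one.

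**The case against.** The case against has real weight.

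- **It is a secondary analysis.** This stands. A reader might infer that the main PHQ result is compromised. The article does not support that: the primary model uses the PHQ-14 alone, and the response-rate comparison uses only the PHQ-14 and the PVSS.
- **The hypotheses concern active relative to sham.** This stands for an additive offset, as steps 1 and 3 show. A reader might infer an inflated false-positive rate for the treatment effect; there is none. A high false-positive rate arises only for a test of acute change within an arm, and section 4.1 specifies no such test. The protection does not extend to unequal sensitivity (step 4).
- **The offset may be close to zero.** This stands. Supplementary Method S4 is not shown and may give a scoring rule that tracks compound ratings well. The simulations return whatever offset is put in and are no evidence of its size. A scoring rule alone would still not establish that the two forms give equal scores.
- **The two might be separable after all.** Partly right. A parametric time curve with an instrument term separates them. So might variation in session dates: with gaps of 2 to 4 days, session 3 can fall on day 6, which puts a PHQ-9 on day 7, where the assumed weekly schedule also has a PHQ-14. Pooled over all possible gaps, a model with free calendar-day effects and an instrument term has full rank (14 of 14). This rests on the one shared day and assumes that response depends on days since the first session, not since the latest one. Both routes need an instrument term, which the article does not mention, and an assumption about the very curve under study.
- **Model terms are commonly left to the SAP.** True in general. Here, however, the article itself states that the two totals are combined and gives alignment as the reason, so that reasoning can be judged as it stands.

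**Conclusion.** The concern holds for the within-arm acute time course in the secondary PHQ re-run. With free time effects, that curve cannot be told apart from the change of questionnaire, and any additive offset enters it one for one. The aliasing does not depend on the assumed SDs or the size of the offset. It does depend on PHQ-9 totals entering only on the days after sessions, as section 4.1 describes.

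The size of the bias cannot be determined from the article: it is 0 if the forms score equally, and it was 1, 2 or 3 points in the simulations only because those shifts were assumed. The primary PHQ-14 model and the response-rate analysis are unaffected. The active-minus-sham contrast remains valid as a test, but if the forms differ in sensitivity its acute size would scale with the ratio (−2.4 to −3.6 for a true −3 at ratios 0.8 to 1.2). This is an interpretive fault in one secondary analysis, worth correcting because time course is a stated aim and the correction is cheap.

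**What to change.** For the secondary analysis in section 4.1:

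1. **Check Supplementary Table S2** to see whether the PHQ-9 is given at baseline and at the end of the study. Section 3.2.2 read with Table 2 makes this probable, not certain.
2. **If it is,** enter those eight-item totals as well and add a fixed instrument effect (PHQ-9 versus PHQ-14). The offset is then estimated where no acute effect is present; a baseline PHQ-9 paired with the baseline PHQ-14 already gives full rank (19 of 19). This assumes an offset that is constant over time and does not correct unequal sensitivity. Alternatively, analyse the eight-item PHQ-9 series as its own outcome against its own baseline, which avoids mixing the two scales.
3. **If it is not,** interpret the day-after points only as active-minus-sham differences and do not present them as a within-arm time course.

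The cost is a sentence in the plan and one model term, with no new data collection if the anchors exist. The downside is slightly wider intervals for the within-arm acute change.

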## 2 Materials and methods

### 2.1 Subject population

This protocol will enroll up to 100 right-handed adult participants with high anhedonia and moderate or high depression, with the goal of achieving an evaluable sample of at least 40 participants. For the purposes of this protocol, evaluable participants are defined as those who complete all three LIFUP sessions, both MRI scans, and at least one outcome measure after completing LIFUP.

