### 3.1 Intervention protocol

#### 3.1.1 Condition assignment

Following screening and enrollment, participants are block-randomized to one of two conditions at equal rates: (1) active stimulation to the left caudate or (2) sham stimulation to the left caudate. A previous version of this protocol block-randomized participants into three conditions at equal rates: (1) active stimulation to the left caudate head, (2) active stimulation to the right nucleus accumbens, or (3) sham (assigned to left caudate or right nucleus accumbens to maintain concealment of conditions); however, due to budget changes, randomization to the “active stimulation to the right nucleus accumbens” condition was removed; a total of six participants were assigned to the active nucleus accumbens condition prior to its removal.

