### 4.2 Analysis of MRI data

Primary imaging analyses will include pre vs. post-LIFUP analysis of reward processing, activation, and connectivity of the caudate and nucleus accumbens as measured with resting state fMRI and task fMRI. Preprocessing of functional MRI data will be done with fMRIprep, Tedana, and XCP-D (Esteban et al., 2020; DuPre et al., 2021; Mehta et al., 2023). Resting state and task fMRI analyses will be conducted using the fMRIB Software Library (FSL) (Woolrich et al., 2001, 2004).

The functional MRI data collected during the Card Guessing Task will be used to assess changes in reward processing across active and sham LIFUP. Reward processing will be assessed by comparing fMRI activation during gain vs. loss trials as well as during gain trials vs. inter-trial intervals. Then, a repeated-measures ANOVA design will be used to assess the effect of time and group on these lower-level contrasts. We hypothesize that participants who received active LIFUP will have higher reward-responsive activity in their respective target regions (i.e., either nucleus accumbens or caudate) compared to those who received sham. This would represent a normalization of activity, as decreased activity has been observed in both regions in response to reward-related tasks (Wang et al., 2021).

Connectivity values between multiple regions of interest will be extracted from the resting state fMRI data in order to investigate changes across LIFUP vs. sham using multi-level modeling. Some particular variables of interest for this analysis due to prior implications for anhedonia in the literature include default mode network average connectivity, left caudate to superior frontal gyrus connectivity, right nucleus accumbens shell to left subgenual anterior cingulate cortex, and right nucleus accumbens core to right precuneus (Dunlop et al., 2019; Liu et al., 2021; Yang et al., 2022).

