This study is also one of the first studies to investigate the effects of multiple sessions of deep brain LIFUP on depressive and anhedonic symptoms; previous multi-session LIFUP studies in clinical populations have found significant impacts on anxiety symptoms (Mahdavi et al., 2023), autism spectrum disorder symptoms (Cheung et al., 2023), and worry symptoms (Reznik et al., 2020). Furthermore, a single, 40-min session of LIFUP to the subcallosal cingulate cortex was recently found to reduce depressive symptoms in individuals with treatment resistant depression (Riis et al., 2024a,b). However, none of these previous studies included longitudinal neuroimaging measures or continuous physiological monitoring. As a result, this study is a critical step forward in the investigation of the potential neurological and physiological effects of multi-session deep brain LIFUP. This is especially important given that most other non-invasive brain stimulation techniques used in psychiatric applications, such as transcranial magnetic stimulation (TMS) and transcranial direct current stimulation (TDCS) require multiple sessions for optimal treatment response (Li et al., 2022; Hutton et al., 2023). While this study still does not reach the 10+ sessions typically used in TMS and TDCS applications, a demonstration of the feasibility and safety of multi-session LIFUP through this protocol would provide support for the investigation of more intensive LIFUP protocols in future studies.

A notable limitation of this study protocol is the timeline variability across participants. The time course of LIFUP effects after multiple consecutive sessions has not yet been investigated and is therefore unknown. Thus, while the 3–14 day window between the last LIFUP session and the post-LIFUP MRI is necessary for the logistical feasibility of the study, there is a chance that the effects observed in the neuroimaging data for each participant may be strongly impacted or even rendered undetectable by the relative timing of the post-LIFUP MRI. This is a critical confound that will need to be controlled for in analyses; however, this range of timepoints may also facilitate investigation of the time course of post-LIFUP changes in neurological function.

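### Repeated-measures ANOVA for two-timepoint outcomes and the Card Guessing Task is valid but less precise than baseline adjustment, uses a weak three-level test for the questionnaires, and names no scan-delay term for imaging

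*Protocol article*

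**What the plan says.** Section 4.1 states that, for secondary outcomes measured twice, "repeated measures ANOVA will be used to investigate the effect of time (pre vs. post-LIFUP) and group". It lists three groups: active caudate, active nucleus accumbens and sham. Section 3.2.2 places these questionnaires at baseline and at the end of the study.

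Section 4.2 says of the Card Guessing Task that "a repeated-measures ANOVA design will be used to assess the effect of time and group on these lower-level contrasts". The task falls under the primary imaging analyses. The stated aim is to assess changes in reward processing across active and sham LIFUP. No covariate is named, and the number of groups is not spelled out.

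The second MRI takes place 3–14 days after the third session (section 3.3). The Discussion says of this variation: "This is a critical confound that will need to be controlled for in analyses".

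The sample is planned "with the goal of achieving an evaluable sample of at least 40 participants", where evaluable means "those who complete all three LIFUP sessions, both MRI scans, and at least one outcome measure after completing LIFUP". Participants are now "block-randomized to one of two conditions at equal rates", and "a total of six participants were assigned to the active nucleus accumbens condition prior to its removal".

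Primary self-report outcomes and resting-state connectivity are to be analysed by multi-level models. The primary self-report analysis pools the two active arms against sham, followed by caudate against sham.

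**The concern.** Three features of the stated model cost information in a trial of about 40 people.

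- **Use of the baseline.** In a pre-post ANOVA the treatment effect is the group-by-time term. It subtracts the whole baseline value, whatever the pre-post correlation. In a randomised comparison, regression on baseline removes only as much as the correlation justifies, so its variance is never larger apart from the degree of freedom spent.
- **Three-level group.** The questionnaire test spreads its power over two degrees of freedom, although one level holds six people. It also departs from the contrasts named for the primary self-report outcomes in the same section.
- **Scan delay.** The Discussion commits the analysis to controlling the delay, but the Card Guessing Task model as described contains only time and group.

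There is also a smaller point. A classical repeated-measures ANOVA drops anyone who lacks one of the two values. An evaluable participant needs only one outcome measure after LIFUP, so some may have no end-of-study questionnaire.

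At stake is the chance of detecting an effect in every two-timepoint secondary outcome and in one primary imaging analysis.

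**Working it through.** **Inputs.** From the protocol: at least 40 evaluable participants, equal allocation, six people in the accumbens arm, scan window 3–14 days. Not given, so assumed: two-sided 5% level, SD 1 at both timepoints, pre-post correlation ρ from 0.3 to 0.9, effect 0.8 SD, and group sizes of 20/20 or 17 caudate, 6 accumbens and 17 sham (17 + 6 + 17 = 40). The protocol states no power or detectable effect, so there is no figure to reproduce.

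**Step 1. Group-by-time equals change score.** On one simulated data set with groups of 17, 17 and 6, the group-by-time F from the repeated-measures ANOVA was 3.262, and the one-way F on the change scores was also 3.262.

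**Step 2. Variance.** Per participant, the change score has variance 2(1 − ρ), and the baseline-adjusted post value has 1 − ρ². The ratio is (1 − ρ²) / [2(1 − ρ)] = (1 + ρ)/2. The detectable difference at 80% power with 20 per arm is (1.96 + 0.84) × √(2/20) × √variance (normal approximation). Power is from the noncentral t distribution at 0.8 SD, with 38 degrees of freedom for change and 37 for ANCOVA.

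| ρ (assumed) | Change variance | ANCOVA variance | Ratio | Detectable difference, change → ANCOVA (SD) | Power at 0.8 SD, change → ANCOVA |
|---|---|---|---|---|---|
| 0.3 | 1.40 | 0.91 | 0.65 | 1.05 → 0.85 | 55% → 73% |
| 0.5 | 1.00 | 0.75 | 0.75 | 0.89 → 0.77 | 69% → 81% |
| 0.7 | 0.60 | 0.51 | 0.85 | 0.69 → 0.63 | 89% → 93% |
| 0.9 | 0.20 | 0.19 | 0.95 | 0.40 → 0.39 | no visible difference |

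With 17 per arm and ρ = 0.5, power is 62% for change and 74% for ANCOVA.

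**Step 3. Three-level test (questionnaires).** Change scores, ρ = 0.5 (so the change SD is 1), groups 17/6/17, caudate effect 0.8 SD:

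- The omnibus F has noncentrality Σn(μ − mean)². With an accumbens effect of 0.8, the overall mean is 23 × 0.8/40 = 0.46, and the noncentrality is 23 × 0.34² + 17 × 0.46² = 6.26. Power on 2 and 37 degrees of freedom is 57%. With an accumbens effect of 0.4 it is 50%, and with 0 it is 57%.
- Caudate against sham has noncentrality 0.8²/(2/17) = 5.44 and power 62% in all three cases.
- Pooled active against sham, accumbens effect 0.8, has noncentrality 0.8²/(1/23 + 1/17) = 6.26 and power 68%. If the accumbens effect is 0, the pooled mean is 17 × 0.8/23 = 0.59, the noncentrality is 0.59²/(1/23 + 1/17) ≈ 3.4, and power is about 44%.

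So the caudate contrast beats the omnibus test in every case. The pooled contrast beats it when both targets work similarly, but not when accumbens does nothing.

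**Step 4. Missing values.** If 6 of 40 post values are missing, repeated-measures ANOVA uses 34 people and so does ANCOVA. A likelihood model on both timepoints keeps all 40.

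**Step 5. Scan delay.** A simulation used 20 per arm, 4,000 runs, delay uniform over 3–14 days and unrelated to arm, and an effect fading linearly to zero at day 14. The mean estimate was 0.80 with or without delay terms. At ρ = 0.5, adding delay and its interaction with arm moved power from 0.65 to 0.67 in the change model and from 0.75 to 0.78 in ANCOVA.

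**The case against.** Repeated-measures ANOVA is a valid analysis of randomised two-timepoint data, and the gain from ANCOVA depends on a correlation that the protocol does not give. At 0.9 the gain is negligible. Both points stand. They limit the size of the concern but not its direction.

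Several stronger readings are tempting, and the document does not support them.

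- **That the baseline is wasted.** It is not. A change score uses it, only less efficiently.
- **That treatment is judged by the group main effect**, which averages in a pre-treatment value and halves the effect. Section 4.2 aims at change across active and sham, which is the group-by-time term. The wording could name the interaction, but the design implies it.
- **That the scan delay is a flaw of the questionnaire analysis.** It concerns MRI only. Nor is it a flat contradiction: the Discussion itself promises control, and a condensed article may leave the full covariate list to the analysis plan. What remains is that the model in section 4.2 does not yet carry out the promise.
- **That omitting delay biases the result.** If delay is unrelated to arm, omitting it adds noise and does not shift the contrast.
- **That baseline adjustment cures everything.** ANCOVA alone deals with neither missing post values nor delay. Delay could be added to either model.
- **That many scan pairs will be lost.** Since "evaluable participants are defined as those who complete all three LIFUP sessions, both MRI scans", few imaging pairs can be lost within the evaluable set, other than through scan quality or a skipped task.
- **That the accumbens arm has been abandoned.** Allocation stopped, but the protocol still states hypotheses for it and expects to analyse its six participants. The third level costs one extra degree of freedom.

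**Conclusion.** The point holds as one of efficiency and consistency, not validity. The planned ANOVA gives a correct test, but for a randomised pre-post comparison of this size the same data support a more precise one. The variance saving is 35%, 25%, 15% or 5% at ρ = 0.3, 0.5, 0.7 or 0.9, assuming equal SDs at both timepoints. Around ρ = 0.5 that is roughly 12 percentage points of power for a 0.8 SD effect with 20 per arm. If these outcomes correlate near 0.9, little is gained.

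For the questionnaires, at ρ = 0.5 and a 0.8 SD caudate effect, the omnibus test loses about 5 to 11 points of power against caudate versus sham. The scan-delay gap is real but small in effect: 2 to 3 points of power in the simulated case, and no bias under the stated assumption.

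The primary self-report and resting-state analyses already use multi-level models and are not affected. The change is worth making because it costs little, and because the Card Guessing Task is a primary imaging analysis.

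**What to change.** 1. **Model.** For the two-timepoint questionnaires and the Card Guessing Task contrasts, define the treatment effect as the post-LIFUP difference between arms adjusted for baseline. Use ANCOVA where post values are complete. Where values are missing, use a likelihood-based model of both timepoints with a common baseline mean, which keeps participants with only one value.
2. **Contrasts.** For the questionnaires, replace the three-level omnibus test with the contrasts already named for the primary self-report outcomes: pooled active against sham, then caudate against sham. Report the six accumbens participants descriptively or as a separate contrast. The pooled contrast is diluted if accumbens stimulation has no effect, so the caudate contrast should always be shown beside it.
3. **Scan delay.** In the Card Guessing Task model, add days from the third LIFUP session to the second scan, centred at its mean so that the arm effect refers to a typical delay and not to day 0. Fit the delay-by-arm interaction as a sensitivity analysis.

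**Cost.** Baseline values and scan dates arise from the planned visits, so no new data are needed. The price is a few degrees of freedom and some extra analysis work. Section 4.2 names FSL for task fMRI, so the team should check that the group-level model can carry these terms there. If it cannot, the model can be fitted to values extracted from the target regions.
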